### Sample size calculation

The sample size for the main iKMC trial was a total of 4200 neonates. Early completion in January 2020 led to a total of 3211 neonates being enrolled in the main iKMC trial. A preliminary review of literature of neurodevelopment in infants between 1 and < 1.8 kg shows the prevalence of any of the conditions of cerebral palsy, hearing impairment, vision impairment, and mean development scores to vary from 5 to 25% [25–27]. Any neurodevelopmental impairment (e.g., cerebral palsy, Bayley score < 85, hearing or vision impairment) in the study population is estimated to be approximately at 15–25%. We estimated the sample size for comparison of the risk of neurodevelopmental impairment in control and intervention groups (20% compared with 15% or 25% [25% lower or higher]) with 80% power and a significance level of 5% to be 1100 per group, requiring a total of about 2200 children.

We thus propose to enroll 2200 babies from the main trial to reach the above-mentioned sample size.

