The schedule of outcome assessments is shown in Table 2. As this is a follow-up study of the main iKMC trial participants, and was initiated in a phased manner in January 2019, approximately 14 months after the start of the parent trial, infants are enrolled on a rolling basis. While all efforts are made to recruit the infant within the first 3 months, participants from the parent trial who have completed 3 months of age prior to the follow-up study start date are recruited after the initial assessment time points. Assessments for outcome measurements are performed at the earliest age-appropriate time point feasible for the individual child upon enrolment for this follow-up study. Due to the challenge posed by the COVID-19 pandemic with ensuing lockdowns and permanent movement of many of the children of migrant laborers to distant areas, the age window for enrolment and completion of all assessments was extended to 36 months, and we switched to telephonic follow-up wherever we could but retained in-person follow-up for the primary outcome measurement at 12 and 24–36 months. This was implemented after due approval from the institutional review boards (IRBs) or ethics committees.

**Table 2 Tab2:** Outcome measurement schedule

Assessment schedule	Discharge	3mo	6mo	9mo	1 yr	15mo	18mo	21mo	2 yr to 3 yr
Motor impairment/cerebral palsy risk			X		X				X
Hearing impairment	X								
Vision impairment					X				
Mental, motor, social-emotional development									X
Epilepsy		X	X	X	X	X	X	X	X
Mortality		X	X	X	X	X	X	X	X
Weight			X		X				X
Infant length/child height			X		X				X
Head circumference			X		X				X
Feeding practices		X	X	X	X	X	X	X	X
Hospitalization admission at least overnight		X	X	X	X	X	X	X	X
Home environment							X		
Maternal depression			X		X				
Approximate duration of the study visit	30 min	30 min	45 min	20 min	60 min	20 min	30 min	20 min	60–90 min

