### General principles for analysis

The analysis will be by intention to treat. The primary outcome is a composite outcome comprising cerebral palsy, hearing impairment, vision impairment, cognitive, language, socio-emotional, adaptive and motor impairment, and epilepsy, and the presence of any one or more will be considered as neurodevelopmental impairment. However, during analyses, we will also consider each of these outcomes individually. Table 1 includes the scale/tool used for outcome measurement and wherever appropriate, the cutoffs of the scales, to indicate the presence or absence of the neurological impairment.

The primary and secondary outcomes will be compared between the intervention and control groups. All planned analysis will use a 5% significance level. Risk ratios and their confidence intervals will be calculated and will be the primary analysis if the loss to follow-up is 2.5% or lower. In case the loss to follow-up for the primary outcome is greater than 2.5%, we will additionally calculate hazard ratios and their confidence intervals. Additionally, we will adjust the results for confounding using multiple logistic regression and Cox proportional hazards models if there are any important differences in baseline characteristics between immediate KMC and control groups.

If more than 5% of data is missing from interim assessments, multiple imputation will be performed, accounting for clustering by country with the number of imputations based on the percentage of missing data. Subgroup analysis will be conducted by (i) birth weight categories (1 to < 1.2 kg, 1.2 to < 1.5 kg, and 1.5 to < 1.8 kg), (ii) gestation (< 34, 34–36, >=37 weeks), and (iii) singleton/multiple birth. Secondary analysis will be limited to an analysis by compliance. This secondary analysis will present the efficacy of the intervention by average duration of skin-to-skin contact over the first 3 days of life, categorized as > =20 h/day, 10–19 h/day, and < 10 h/day.

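### The 2200 to be enrolled equals the number that must be evaluable to detect a rise from 20% to 25%, so any appreciable loss takes power in that direction below the stated 80%

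*Protocol article*

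**What the plan says.** The section Sample size calculation takes a control rate of 20% and considers a change in either direction: "20% compared with 15% or 25% [25% lower or higher". It gives the requirement as "with 80% power and a significance level of 5% to be 1100 per group, requiring a total of about 2200 children". The next sentence makes the enrolment target the same number: "We thus propose to enroll 2200 babies from the main trial to reach the above-mentioned sample size". The section mentions no margin for loss, death or missing outcome.

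Elsewhere the article shows that some enrolled children will not reach the last assessment:

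- The text around Table 2, in Primary and secondary outcomes, reports lockdowns and "permanent movement of many of the children of migrant laborers to distant areas".
- Table 1 lists death between 29 days and 3 years as a secondary outcome, and places the Bayley assessment at 24 to 36 months.
- General principles for analysis has a conditional rule: "In case the loss to follow-up for the primary outcome is greater than 2.5%, we will additionally calculate hazard ratios". This is the only figure for loss to follow-up in the article. It triggers an analysis and does not state an expected rate.

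**The concern.** A power calculation gives the number of children whose outcome is known. If enrolment is set at that number, the stated power holds only when almost every enrolled child is classified. Follow-up here runs to 3 years of age in five countries, through a pandemic.

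The article claims 80% power in both directions, and the upward one is not incidental. The Abstract asks whether better survival might bring more neurodevelopmental morbidity, and the Background notes concern about increased impairment. The upward comparison needs more children, so it fixes the size, and it is also the one left without a margin. What is at stake is the accuracy of the stated power for detecting harm.

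**Working it through.** **Inputs, from Sample size calculation.** Control rate 20%; alternatives 15% and 25%; power 80%; significance 5%; 1100 per group. Sidedness is not stated. Two-sided is taken because both directions are considered and because the one-sided formula gives 862 for 20% against 25%, far from 1100.

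**Formula (pooled variance, no continuity correction).** With p̄ = (p1 + p2)/2,

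n per group = [1.960·√(2p̄(1−p̄)) + 0.842·√(p1(1−p1) + p2(1−p2))]² / (p1−p2)²

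**Reproducing the article's figure.**

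- 20% against 25%: p̄ = 0.225, so n = (1.1575 + 0.4961)² / 0.05² = 1093.7, that is 1094 per group (2188 in total). This rounds to the stated 1100.
- 20% against 15%: p̄ = 0.175, so n = (1.0532 + 0.4513)² / 0.05² = 905.4, that is 906 per group.

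Other usual formulas for 20% against 25% agree: 1091 (unpooled), 1092 (arcsine) and 1104 (log risk ratio). With continuity correction it is 1134, above the stated size. The rise to 25% therefore sets the 1100.

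**Slack in 1100 per group.**

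- Rise to 25%: 1 − 1093.7/1100 = 0.6%.
- Fall to 15%: 1 − 905.4/1100 = 17.7%.

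**Power after loss.** The evaluable number per group is n = 1100 × (1 − loss), with equal loss in both groups, and

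power = Φ{ [0.05·√n − 1.960·√(2p̄(1−p̄))] / √(p1(1−p1) + p2(1−p2)) }

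| Loss (assumed) | Evaluable per group | Power, 20% v 25% | Power, 20% v 15% |
|---|---|---|---|
| 0% | 1100 | 80.2% | 87.0% |
| 2.5% | 1072 | 79.2% | 86.2% |
| 5% | 1045 | 78.2% | 85.3% |
| 10% | 990 | 76.0% | 83.4% |
| 15% | 935 | 73.6% | 81.3% |
| 20% | 880 | 71.0% | 78.9% |

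**Rate detectable with 80% power.** Solving the same formula for the higher rate against 20% gives 25.0% at no loss, 25.1% at 5%, 25.3% at 10% and 25.6% at 20%.

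**Available pool.** The Background gives 1609 and 1602 infants randomised, with neonatal mortality of 12.0% and 15.7%. Survivors number about 1609 × 0.880 + 1602 × 0.843 = 1416 + 1350 = 2766. Keeping 1094 evaluable per group would need 1094/0.90 = 1216 per group (2432 in total) at 10% loss, and 1094/0.80 = 1368 per group (2736) at 20%. Those totals are about 88% and 99% of the survivors.

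**The case against.** The strongest reply is that the study is planned to show benefit. The Background names reduced impairment as the main hypothesis, and for that comparison 1100 per group already leaves room for about 17.7% loss. This stands. A reader might infer that the study is underpowered for its main question; the figures do not support that unless loss passes that level.

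Other parts of the reply also stand:

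- **Practical size.** The detectable rate moves by 0.3 points at 10% loss and 0.6 points at 20%. The planning range for any impairment is itself 15 to 25%.
- **Loss rates.** The 2.5% threshold could be read as a forecast of loss. It is only a conditional trigger, and every loss rate above is an assumption.
- **Countermeasures.** The article extended the window to 36 months, used telephone contact where possible and kept in-person visits for the primary outcome. Rolling enrolment also shortens the period at risk of loss for some children.
- **Composite outcome.** One positive component classifies a child as impaired, and hearing, vision, the 12-month neurological examination and epilepsy screening come before the last visit. Treating every lost child as non-evaluable is a simplification. It remains apt for children lost without a positive finding.
- **Multiple births.** One might add a power penalty for correlated siblings. The article does not give the proportion of multiples or say how siblings were allocated, so not even the direction of that effect can be established.
- **Reading a null result.** One might argue that a null result would be taken as excluding harm. Risk ratios with confidence intervals are planned, and the intervals will show what is excluded whatever the design power.

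What the reply does not remove is that the article states 80% power in both directions and equates the enrolled with the evaluable number. Eligibility of all consenting survivors leaves room above 2200, but the article does not say that the target will be exceeded.

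**Conclusion.** The point holds in a limited form. The 1100 per group is the uninflated requirement for 20% against 25%, and enrolling exactly that many delivers 80% power for a rise only if loss stays below about 0.6%. The shortfall is under 2 points up to 5% loss, about 4 points at 10% and about 9 points at 20%.

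These figures rest on a two-sided 5% test, the pooled-variance formula, equal loss in both groups, lost children counted as non-evaluable, and assumed loss rates. The effect is modest and confined to the harm direction. The paragraph should still be corrected, because it states a power that the enrolment target does not deliver in one of the two directions it names.

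**What to change.** Restate the paragraph in Sample size calculation so that it says:

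1. 1100 per group is the evaluable number for 20% against 25%, without inflation for loss or death, and 906 per group suffices for 20% against 15%.
2. The power in each direction over a stated range of loss (for example 0 to 20%, as tabulated above), or at the actual evaluable number once it is known.
3. The rate detectable with 80% power at that number, about 25.3% at 10% loss and 25.6% at 20%.

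The cost is a few sentences and a short recalculation. No extra enrolment, visit or procedure is needed.

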### The intervention

The proposed study is a follow-up of the already concluded randomized controlled trial for evaluating the effect of immediate KMC on infant survival. The intervention and control groups were assigned during the main iKMC trial where KMC is defined as continuous skin-to-skin contact with mother or her surrogate aiming for at least 20 h per day, support for exclusive breastfeeding, and required medical care without separation from the mother as much as possible.

In the intervention group, the mother and baby remained in skin-to-skin contact from the time of randomization whereas the newborns randomized to the control group received conventional care, and the mother and baby were separated until the baby was clinically stable. The details of intervention and control arms and care of the newborns in both the groups are described in the already published protocol paper [11].

### Care of children in both intervention and control groups for the follow-up study

For the ongoing follow-up study, care of the children continues to be as per each site’s routine policy and standard of care, including routine health monitoring visits, care for acute illnesses, and management of morbidities including neurodevelopment impairments. This includes appropriate early diagnosis and management of the neurodevelopmental outcomes of interest. Children with suspicion of epilepsy are referred to appropriate neurologic or child health services for confirmation and management according to national protocols. Those with motor impairments are referred to local rehabilitation specialists for physical therapy as per local resource availability. For any child with signs of developmental impairment (motor, cognitive, or social-behavioral), referral to appropriate early stimulation programs is provided. Early monitoring for vision and hearing impairment is performed routinely and in case of any suspicion, the children are referred to appropriate ophthalmologic and audiology or otolaryngology specialists for appropriate management and to adapt to environment. For every child that has been identified as having neurodevelopmental impairment, each site in line with their standard protocol for the identification, assessment, management, and follow-up care develops an individual care plan (including rehabilitation, psychosocial support, etc.) in consultation with the child’s parents.

### Primary and secondary outcomes

The primary outcome of the follow-up study is the presence of neurodevelopmental impairments assessed by the age of 3 years in all enrolled children. The study duration and window for the last outcome assessment were extended from 2 to 3 years after ethics approval, due to the COVID-19 pandemic. Specifically, this composite outcome includes rates of motor impairment and risk of cerebral palsy, hearing impairment, vision impairment, cognitive, language, motor, socio-emotional or adaptive behavior, and epilepsy and the presence of any one or more will be considered as neurodevelopmental impairment. Secondary outcomes include growth and feeding practices, mortality and home environment (maternal depression and parent–child interactions), and rates of overnight hospital admissions.

Outcomes are assessed via standardized tools and questionnaires (Table 1). Motor impairment and risk of cerebral palsy are measured by standardized neurologic evaluation, using a validated tool, Hammersmith Infant Neurological Examination (HINE) at 6 months, 1 year, and 2 years of age. Cognitive, language, motor, socio-emotional, or adaptive behavior is assessed using Bayley Scales of Infant and Toddler Development (BSID III) at 2 to 3 years of age. Epilepsy is diagnosed using a standardized questionnaire, with operationalization of the International League against Epilepsy (ILAE) definition. Hearing is evaluated at discharge from the hospital or as soon as possible after enrolment in the follow-up study. First, an assessment by screening auditory brainstem responses (ABR) is performed at the facility. If the infant clears this assessment, no further assessment for hearing is required. In case the infant fails this initial screening, he/ she is referred to the audiologist or specialist for re-screening including a diagnostic ABR if required. Visual acuity is measured using Teller Acuity Cards, at or any time after 1 year of age at the facility.

**Table 1 Tab1:** Outcome measurements

Outcomes	Tool	Measurement strategy	Rationale
**Primary outcome**			
Developmental delay	Bayley Scales of Infant and Toddler Development III (BSID III) The scale is used to assess language, cognitive, motor, social-emotional, and general adaptive functions	Assessment by Bayley-trained clinical psychologist/clinician between 24-and-36-month chronological age The BSID III scores will be calculated using corrected gestational age For the BSID III, the composite score range in different domains is as follows: Cognitive: 55–145 Language: 47–153 Motor: 46–154 Social-emotional: 55–145 Adaptive: 40–160 Composite score in each individual domain may be converted into scaled scores that range from 1 to 19. Average scaled scores are between 8 and 12 A composite score of < 80 will indicate developmental delay	BSID III has been developed in the USA and used in LMIC countries, including India [28–31] BSID III, in comparison to BSID II, requires a higher cutoff score for comparable sensitivity in detecting developmental delay. BSID III combined scores < 80 and cognitive and language scores < 85 were found to correlate with BSID II Mental Development Index (MDI) scores < 70 and clinically to moderate-severe developmental delay [31]
Cerebral palsy	Hammersmith Infant Neurological Examination (HINE)	Standardized neurological assessment using HINE at 6, 12, and 24 months According to a recent systematic review [32], HINE scores have 90% predictive accuracy of cerebral palsy By 12 months, a score of < 40 is predictive of non-ambulatory cerebral palsy [plegic, not walking] and a score of 40–60 is predictive of ambulatory cerebral palsy [able to walk], with any score < 70 considered abnormal. The maximum score is 78 The accepted norms will be used for the cutoff in this study, which are > 70 at 6 months and > 73 at 12 months and older [32–37] Due to the risk of more subtle findings, particularly in premature infants, there is increased sensitivity to the tool when used at multiple time points; therefore, the examination will be performed at an additional time point of 2 years For the primary outcome, the score at the 12- and 24-month assessments will be considered	HINE is a strongly recommended scale for early diagnosis of cerebral palsy [32] It is a standardized and scorable clinical neurological examination that is applicable for infants aged between 2 and 24 months and has been shown to be an easy-to-train tool with interobserver reliability even in less experienced staff [38]
Hearing impairment	Hearing assessment measured ideally at discharge or as soon as possible at enrolment or first follow-up	First assessment by screening auditory brainstem responses (ABR) If screening ABR is passed, no need for further hearing assessment tests In case screening ABR is failed, the participant is referred at the earliest possible opportunity to audiologist or specialist for re-screening, including, diagnostic ABR as applicable. Hearing impairment is defined as failed diagnostic ABR or failed re-screening ABR if diagnostic ABR is not available	International guidelines recommend hearing assessment within the first month of life whenever feasible [39] While Otoacoustic Emission (OAE) screening can be used in settings where ABR is not available, it is less preferred due to the potential for missing retro-cochlear hearing loss. Therefore, in studying high-risk infants, ABR is preferred [39–42]
Vision impairment	Structural visual examinations, including for retinopathy of prematurity, will be performed between discharge and 3 months, with visual acuity measured at 12 months	Visual acuity measured by Teller Acuity Cards at the facility Impairment defined by measurements 2 lines less than age-defined normative values	Teller Acuity Cards will be used due to the availability of age-specific reference ranges [43, 44]
Epilepsy	Screen for seizure at each follow-up visit. If screening positive, refer to a clinician	First assessment by epilepsy screening questionnaire at each follow-up visit If the participant screen negative, there is no need for further assessment tests In case the participant is screened positive, he/she will be assessed by a pediatrician/pediatric neurologist by a diagnostic questionnaire to arrive at a diagnosis of epilepsy/no epilepsy using the ILAE definition [45]. To reduce variability in diagnosis for purposes of this study, the ILAE diagnostic criterion has been operationalized for this study in the diagnostic questionnaire as either 2 unprovoked seizures separated by at least 24 h or 1 unprovoked seizure and one other positive finding of neurodevelopmental impairment	Screening questionnaires for pediatric epilepsy are limited due to small populations and limited age range and have demonstrated moderate validity [46, 47] A questionnaire comprised from validated pediatric epilepsy screening questionnaires and agreed upon by pediatric neurologists from the participating sites has been employed after local pilot testing
**Secondary outcomes**			
Mortality	Screen for death of enrolled child occurring any time between 29 days and 3 years of age	Mortality/survival status at each screening point. Assessments performed every 3 months until the age of 3 years	
Growth	Anthropometric parameters of weight (W), length (L), and head circumference (HC) for age using standardized equipment	Anthropometry at 6, 12, and 24 months of age. Parameters are plotted as per corrected age on WHO Multicentre Growth Reference Study (MGRS) charts and interpreted as per *z* scores Postnatal growth failure defined as fall in *z* scores or *z* scores < 2 SD	Measurements are obtained during facility visits. In case the participant is unable to visit the facility, we perform the measurement at the home of the participant
Feeding practices	Assessment of breastfeeding, expressed breast feeds, complementary feeds at 6 months, and adequacy of feeding beyond infancy	Feeding practices measured through a standard questionnaire at each follow-up visit—every 3 months until the age of 3 years	
Maternal depression	Patient Health Questionnaire 9 (PHQ-9)	Maternal depression measured using PHQ-9 at 6 and 12 months of age	Literature suggests, while early screening for post-partum depression is important, additional screening points at either 6 or 12 months can capture additional women who may have initially screened negative at earlier time points. Therefore, we have included these time points in this study [48]
Home environment	HOME	Assessment of home environment measured using standard HOME-SF scale at 18 months by a home visit	HOME is a validated tool across cultures. The HOME-SF scale has 6 subscales: (1) parental responsivity, (2) acceptance of the child, (3) organization of the environment, (4) learning materials, (5) parental involvement, and (6) variety in experience These align with the MAL-ED study which has also identified that a three-factor structure—emotional and verbal responsivity, clean and safe environment, and child cleanliness—can be examined cross-culturally [49]

The schedule of outcome assessments is shown in Table 2. As this is a follow-up study of the main iKMC trial participants, and was initiated in a phased manner in January 2019, approximately 14 months after the start of the parent trial, infants are enrolled on a rolling basis. While all efforts are made to recruit the infant within the first 3 months, participants from the parent trial who have completed 3 months of age prior to the follow-up study start date are recruited after the initial assessment time points. Assessments for outcome measurements are performed at the earliest age-appropriate time point feasible for the individual child upon enrolment for this follow-up study. Due to the challenge posed by the COVID-19 pandemic with ensuing lockdowns and permanent movement of many of the children of migrant laborers to distant areas, the age window for enrolment and completion of all assessments was extended to 36 months, and we switched to telephonic follow-up wherever we could but retained in-person follow-up for the primary outcome measurement at 12 and 24–36 months. This was implemented after due approval from the institutional review boards (IRBs) or ethics committees.

**Table 2 Tab2:** Outcome measurement schedule

Assessment schedule	Discharge	3mo	6mo	9mo	1 yr	15mo	18mo	21mo	2 yr to 3 yr
Motor impairment/cerebral palsy risk			X		X				X
Hearing impairment	X								
Vision impairment					X				
Mental, motor, social-emotional development									X
Epilepsy		X	X	X	X	X	X	X	X
Mortality		X	X	X	X	X	X	X	X
Weight			X		X				X
Infant length/child height			X		X				X
Head circumference			X		X				X
Feeding practices		X	X	X	X	X	X	X	X
Hospitalization admission at least overnight		X	X	X	X	X	X	X	X
Home environment							X		
Maternal depression			X		X				
Approximate duration of the study visit	30 min	30 min	45 min	20 min	60 min	20 min	30 min	20 min	60–90 min

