### Study population

All infants born with birth weight between 1.0 and < 1.8 kg, enrolled in the main trial, who survive the neonatal period, and whose parents consent for their participation in the follow-up study, are eligible to be enrolled.

All infants who die within the first month of life or whose parents refuse consent for follow-up will be excluded from the study.

We employ two strategies to approach the parents for enrolment. First, we approach the mother/parent during the 29-day follow-up visit for the main trial. The second strategy is for children who have completed the 29-day follow-up visit in the main trial. For these children, we approach the mother/parent either telephonically or when they visit the high-risk infant follow-up clinic as part of standard hospital care. A verbal preconsent is taken and an in-person hospital visit is scheduled for a detailed written informed consent for participation in the follow-up study.

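### Mortality is defined from 29 days but only in enrolled children, many enrolled months later, so deaths before enrolment go uncounted and absolute mortality is understated in both arms

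*Protocol article*

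**What the plan says.** The Mortality row of Table 1 gives the outcome as "Screen for death of enrolled child occurring any time between 29 days and 3 years of age". The window opens at 29 days, and the population is children who have been enrolled.

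The text introducing Table 2 says the follow-up study was "initiated in a phased manner in January 2019, approximately 14 months after the start of the parent trial". It adds that parent-trial participants "who have completed 3 months of age prior to the follow-up study start date are recruited after the initial assessment time points", and that after the pandemic began "the age window for enrolment and completion of all assessments was extended to 36 months".

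Under Study population, children who had already passed their 29-day visit are reached by a second route: "we approach the mother/parent either telephonically or when they visit the high-risk infant follow-up clinic". Written consent is then taken at a hospital visit. The only exclusions named are death in the first month and refusal of consent.

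Under General principles for analysis, the plan states: "Risk ratios and their confidence intervals will be calculated and will be the primary analysis". That sentence is conditional on loss to follow-up of 2.5% or lower. Above that level for the primary outcome, hazard ratios are added. No time origin or entry-time rule is given.

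**The concern.** For a child enrolled at the 29-day visit, the window and the population agree. For a child first reached at, say, 10 months, they do not: that child had to be alive to be enrolled, so the preceding nine months could not contain a counted death. A similar child who died at 4 months never enters the numerator or the denominator.

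A simple proportion of deaths among enrolled children, labelled as 29 days to 3 years, would therefore be too low. A survival model with its clock started at 29 days for everyone would treat the pre-enrolment time as observed. The 2.5% rule offers no protection, because a child who died before being approached was never enrolled and so is not lost to follow-up.

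The Background section names mortality beyond the neonatal period as part of the evidence for policy change. After a neonatal mortality difference of 12.0% against 15.7%, readers will look to this outcome to see whether the gain lasts.

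**Working it through.** The article gives no figure for the mortality outcome, so there is none to reproduce. The check asks how common late entry must be, how many deaths it hides, and what it does to the arm comparison.

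**Inputs from the article.** 1609 and 1602 infants, with neonatal mortality of 12.0% and 15.7% (Background); parent trial completed January 2020 and target cohort 2200 (Sample size calculation); follow-up begun January 2019, about 14 months into the parent trial (text introducing Table 2). This implies about 14 + 12 = 26 months of parent-trial accrual.

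**Assumptions not in the article.** Uniform accrual, the shape of the post-neonatal hazard, the start-up lag, and the risk and effect sizes in step 3.

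**1. How many must enter late**
- Neonatal survivors: 1609 × 0.880 + 1602 × 0.843 = 1416 + 1350 ≈ 2766.
- Already past 3 months at study start: (14 − 3)/26 = 42%, or about 1170. The remaining 1596 were younger or not yet born.
- A cohort of 2200 therefore needs at least 2200 − 1596 = 604 children (27%) enrolled after 3 months.
- This depends on accrual. If only 30% of survivors were past 3 months at the start, the minimum falls to about 264; at 20% it is 0. The article nevertheless says that such children are recruited.

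**2. Share of deaths that cannot be counted**

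Suppose every survivor is enrolled as early as possible: at 1 month, or at study start if already older. With F(a) the share of deaths between 1 and 36 months that occur before age a, the uncounted share is (1/26) × ∫ F(a) da, from a = 1 to 14.
- Constant hazard, F = (a − 1)/35: 13²/(2 × 35)/26 = 2.414/26 = 9%.
- Weibull shape 0.5, F = (√a − 1)/5: 4.251/26 = 16%.
- Hazard proportional to 1/age, F = ln a/ln 36: (14 ln 14 − 13)/3.584/26 = 6.683/26 = 26%.

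If every site opened 6 months late, the upper limit becomes 20 and the shares are 20%, 31% and 44%. The constant-hazard integral is also the share of 1-to-36-month person-time that precedes enrolment: about 9% with no lag.

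**3. Effect on the arm comparison**

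Take a hazard c/a with control risk 5.8% from 1 to 36 months, so c = −ln(0.942)/ln 36 = 0.0167.
- *Hazard ratio 0.70 confined to 1–6 months.* Intervention cumulative hazard 0.0167 × (0.70 ln 6 + ln 6) = 0.0508, risk 4.95%, true risk ratio 4.95/5.80 = 0.85. Among enrolled children the risks are 3.861% and 4.356% with no lag (ratio 0.89), and 3.013% and 3.313% with a 6-month lag (ratio 0.91).
- *Hazard ratio 0.70 throughout.* True risk ratio 4.096/5.800 = 0.706. Among enrolled children it is 3.067/4.356 = 0.704 with no lag and 2.327/3.313 = 0.702 with a 6-month lag.

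In both scenarios the control risk of 5.8% appears as 4.4% (no lag) or 3.3% (6-month lag). The ratio moves only when the effect is early.

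**4. What delayed entry does and does not repair**

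In the early-effect scenario, a Cox model with delayed entry gives a pooled hazard ratio of 0.883 (no lag) to 0.908 (6-month lag). It corrects the person-time, but the early deaths remain unobserved.

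**The case against.** The strongest reply is that late entry cannot favour an arm. Allocation was randomised at birth, and delay in entry comes from the calendar date at which follow-up opened. This is left truncation common to both arms, not immortal time attached to one treatment. That stands. A reader might infer from the mismatch that the mortality comparison is pulled towards no difference. The documents do not support that as a general statement: it needs an effect concentrated in the early months, which nothing in the article establishes, and a constant effect comes through unchanged.

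The 20% to 44% figures should not be read as a likely range. They apply a 6-month lag to every site, whereas the article says only that the start was phased and that the first participant was recruited on 11 January 2019.

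Time origin and entry handling in a Cox model are commonly left to the SAP. This also stands: the article does not say that the clock starts at 29 days, and the point does not rest on assuming so. However, the outcome's window and population are fixed in Table 1, and no entry rule can put never-enrolled deaths back into a simple proportion.

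Finally, the exclusions do not expressly bar an infant who died after the first month but before being approached. Enrolment nevertheless requires parental consent to the child's participation at an in-person visit, which in practice means a living child.

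**Conclusion.** The concern holds as a mismatch between the outcome window and the enrolled population. The firm consequences are an understated 29-day-to-3-year absolute mortality in both arms and a comparison conditional on survival to enrolment. With uniform accrual over 26 months and no lag, about 9% to 26% of deaths in the window would go uncounted, depending on how steeply the hazard falls with age. The share is larger where sites opened later and smaller if parent-trial accrual was back-loaded. Dilution of the risk ratio is conditional on an early effect, as in 0.85 appearing as 0.89 to 0.91; it is not an established bias. Children enrolled at the 29-day visit are unaffected. This is a secondary outcome, and the change should be made before mortality is analysed.

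**What to change.** - Analyse mortality as time to death on the age scale, with each child joining the risk set at age of enrolment and censored when last known alive. Report absolute mortality from that left-truncated analysis.
- Restate the outcome in Table 1 as mortality after enrolment, and do not present a simple risk ratio in enrolled children as 29-day-to-3-year mortality.
- Add a sensitivity analysis restricted to children enrolled at or near the 29-day visit, for whom the stated window is observed.
- Where vital status was or can still be recorded at invitation contacts, report deaths before enrolment by randomised arm among the approximately 2766 neonatal survivors.

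The first three items change only the analysis and its wording, and need only each child's enrolment date. Their price is slightly wider intervals, and delayed entry alone does not recover an early effect lost with the unobserved deaths. The fourth item needs a data field and ethics agreement. It may be only partly feasible: parent-trial recruitment ended in January 2020, assessments were due to finish by July 2022, and many families had moved away. Any gaps in vital status should be reported by arm.
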